### Sample size

Sample size calculations are based on 350 consented participants from each of the 12 intervention and 24 control practices, and the assumption that 85% of participants per intervention practice will be screened. This will provide a 90% power at 5% significance level to detect a 1.1% absolute difference in the frequency of diagnosis of new AF between intervention and control practices, assuming 3% newly diagnosed AF is detected in screened patients^42^ and an intraclass correlation coefficient of 0.001.

Sending the heath questionnaire to 1800 participants will give us 90% power to detect a 4 point difference in the Spielberger questionnaire, assuming 60% respond—the rate achieved in the SAFE trial.^60^

### Data collection

#### Baseline data collection

Baseline data detailed in table 3 will be collected from the GP electronic medical records for all individuals who have consented to participate in the trial.

**Table 3 T3:** Baseline participant data to be collected for the safer pilot study

Category	Variable collected
Demographics	Age
	Sex
	Ethnicity
	Index of Multiple Deprivation based on participant postcode
Comorbidities	Atrial fibrillation
	Stroke or transient ischaemic attack
	Coronary heart disease
	Peripheral arterial disease
	Heart failure
	Hypertension
	Diabetes mellitus
	Stroke or transient ischaemic attack
	Dementia
	Depression
Clinical scores and indices	CHA_2_DS_2_-VASc score
	HAS-BLED score
	ORBIT score
	Frailty index
Other variables	Height
	Weight
	Alcohol intake
	Smoking status
	SARS-CoV-2 PCR result

CHA2DS2-VASc, scoring system to assess the risk of stroke in those with AF; HAS-BLED, scoring system to assess the risk of bleeding in those who take anticoagulation for AF; ORBIT, scoring system to assess the risk of bleeding in those who take anticoagulation for AF

#### Follow-up data

This section excludes outcomes for the main trial, which will be detailed in the main trial protocol.

##### Atrial fibrillation

New diagnoses of AF picked up in both intervention and control practices since screening initiation using GP electronic data.Positive diagnoses of AF identified by screening (intervention practices only).

##### Uptake of anticoagulation

For patients diagnosed with AF, whether or not they are prescribed anticoagulation (intervention and control practices) using GP electronic data.Initiation of anticoagulation in AF detected through screening programme (intervention practices only).

##### Process variables

Whether patients agree to screening (intervention practices only).Whether patients are screened (intervention practices only).

##### Psychological outcomes

The psychological effects of screening and impact on functional status will be assessed by comparing responses to the Spielberger State-Trait Anxiety Inventory (STAI) short form,^61^ EQ-5D-5L (EuroQol - 5 Dimensions - 5 Levels)^62^ and SF-8 (Short Form-8).^63^ Changes in responses over time in both groups will be quantified as well as comparisons of responses according to uptake and outcome of screening. These generic measures may be relatively insensitive to some potential specific impacts of screening for AF, but as they do not include reference to the screening programme they enable comparison between screening and control groups. Furthermore, they facilitate comparisons with screening programmes for other conditions, and with other unrelated health service interventions. The questionnaires will be posted to a random (MS Access RND function) sample of participants (126 per intervention practice and 36 per control practice, matched for age (70–73; 74–77; 78 years and over) and sex in six groups. The target numbers in the intervention arm are raised from our sample size calculation to increase the data available from participants who screen positive. Questionnaires will be posted to the screening group alone at baseline (pre-invitation to screening). Both groups will receive questionnaires after 8 weeks and 6 months.

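### The intervention questionnaire sample is enlarged to gain screen-positive respondents, but a random pre-screening draw cannot favour them; on the plan's rates it yields about 23 with new AF, against about 64 if all were sent it.

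*Protocol article*

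**What the plan says.** Under Sample size, the questionnaire study is planned on a total: "1800 participants will give us 90% power to detect a 4 point difference in the Spielberger questionnaire", with 60% expected to respond. No SD, allocation between arms or intraclass correlation is given for this calculation.

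Under Psychological outcomes, the numbers posted are "126 per intervention practice and 36 per control practice", and the intervention figure is explained as "raised from our sample size calculation to increase the data available from participants who screen positive". The selection method is stated: "The questionnaires will be posted to a random (MS Access RND function) sample of participants", balanced over six age and sex groups. The intervention arm alone gets a baseline questionnaire, before the invitation to screening. Both arms are then mailed at 8 weeks and 6 months. The analysis is to include "comparisons of responses according to uptake and outcome of screening".

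**The concern.** The means does not fit the stated purpose. The sample is fixed before anyone's screening result exists, so enlarging it adds positives only in proportion to their frequency, which on the plan's assumptions is about 2.55% of those sampled (0.85 x 0.03) for new AF. Several hundred more people are mailed three times each to gain roughly ten respondents of the kind wanted.

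Psychological impact is one of the pilot's stated aims, and people told that they have AF are an obvious group in which to look for it. If the comparison by screening outcome rests on about two dozen positives, a null result there could be read as reassurance when it mainly reflects small numbers. An analysis plan cannot repair this later, because people who were never mailed cannot be analysed.

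**Working it through.** **Inputs from the protocol article.** Practices and cluster size: "350 consented participants from each of the 12 intervention and 24 control practices" (Sample size), hence 350 x 12 = 4200 intervention participants. Screened 85% and new AF among screened 3% (Outcomes, Box 1). Response 60% (Sample size).

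**1. The plan's own figure.** 1800 cannot be reproduced without an SD; it can only be back-solved. Assuming a two-sided 5% level, a 900/900 split and no clustering, there are 540 respondents per arm:

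SD = 4 / [(1.960 + 1.282) x sqrt(2/540)] = 20.3.

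With a 600/1200 split, or an intraclass correlation up to 0.01, the implied SD lies between about 17 and 20.

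**2. Numbers posted.** Intervention 126 x 12 = 1512; control 36 x 24 = 864; total 2376.

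**3. Expected respondents with screen-detected new AF.** 1512 x 0.85 x 0.03 x 0.60 = 23.1 (binomial 95% range 14 to 33). This applies one rate to all age and sex groups, as the article gives none by group.

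**4. Gain from the enlargement.** This depends on the unstated intervention share of the 1800:

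| Intervention base | New-AF respondents | Gain at 1512 |
|---|---|---|
| 600 (1:2 split) | 9.2 | 14.0 |
| 864 (equal to control) | 13.2 | 9.9 |
| 900 (equal split) | 13.8 | 9.4 |
| 936 (1800 - 864) | 14.3 | 8.8 |

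From a base of 900, the extra 612 people receive 612 x 3 = 1836 mailings.

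**5. Wider definition of positive.** If known AF and other findings brought the total positive rate to 4%, 5% or 6% (assumed), respondents would number 30.8, 38.6 or 46.3.

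**6. Power and precision for 4 points, new-AF positives against screen-negatives.** Screen-negative respondents: 1512 x 0.85 x 0.97 x 0.60 = 748 (this counts everyone screened without new AF). SE = SD x sqrt(1/n + 1/748); power = Phi(4/SE - 1.96); half-width = 1.96 x SE. The SDs of 8 to 15 are assumptions; 20.3 is from step 1.

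| SD | n = 23: half-width, power | n = 64: half-width, power |
|---|---|---|
| 8 | 3.3, 66% | 2.0, 97% |
| 10 | 4.1, 47% | 2.6, 87% |
| 12 | 5.0, 35% | 3.1, 73% |
| 15 | 6.2, 24% | 3.8, 54% |
| 20.3 | 8.4, 15% | 5.2, 33% |

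**7. Mailing every other new-AF positive.** Intervention participants outside the random sample: 4200 - 1512 = 2688. Positives among them: 2688 x 0.85 x 0.03 = 68.5. Mailings at two time points: 137. Respondents: 68.5 x 0.60 = 41.1. Total: 23.1 + 41.1 = 64.3.

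**The case against.** The article promises only more data from screen-positive participants, and going from about 900 to 1512 does raise their expected number by 68%. It claims no power for this subgroup. The literal aim is met, though inefficiently.

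The count of 23 covers new AF only. The article treats AF or other diagnoses as positive and enrols people with known AF who are not anticoagulated, so 23 is a lower figure for all positives. That stands, but targeted mailing would scale up in the same proportion.

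The power figures use a single follow-up score. If baseline and follow-up correlated at 0.6 (an assumption) and all 23 had a baseline, the effective SD would be multiplied by sqrt(1 - 0.36) = 0.8. An SD of 10 would then act like 8 (power 66% rather than 47%) and 15 like 12 (35% rather than 24%). This narrows the shortfall without closing it.

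Targeted mailing is not a full cure: at an SD of about 20, power reaches only 33%. Qualitative work also contributes evidence on harms.

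A reader might infer that the plan will have no usable estimate of anxiety after a positive screen. The article does not support that: it states no SD, and the half-width runs from about 3 to 8 points, which is imprecise but not worthless. A reader might also see a contradiction between 1800 and 2376. There is none, because the article says the intervention numbers were deliberately raised above the calculation.

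**Conclusion.** The point holds as one of efficiency. Random enlargement before screening is a poor way to reach the plan's stated purpose. On the plan's own rates it gives about 23 respondents with screen-detected new AF, about 9 to 14 of them owed to the enlargement. That is too few to detect 4 points reliably unless the SD is well below 10 or baseline adjustment helps a good deal. Sending the follow-up questionnaires to all new-AF positives would give nearly three times as many.

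The counts rest on the plan's 85%, 3% and 60%. The gain rests on the unstated split of 1800, and the power on an assumed SD. This is a cheap improvement to the sampling scheme; nothing here undermines the comparison between arms.

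**What to change.** Keep the planned random sample of 126 per intervention practice, with its baseline questionnaire. In addition, send the 8-week and 6-month questionnaires to every other intervention participant with a positive result, after the practice has told the participant of it. The trial team sends the results to the practices, so it can identify these people. State which result categories count as positive.

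Leave the added participants out of the between-arm comparison, or include them with inverse-sampling-probability weights worked out by practice and age-sex group. Base analyses of change over time on the random sample only.

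The cost for new AF is about 137 extra mailings. At an assumed total positive rate of 6% it would be about 274 (2688 x 0.85 x 0.06 = 137 people, mailed twice). The drawback is that the added participants have no pre-invitation baseline. The control arm has none either, so comparisons of 8-week and 6-month scores do not depend on it.

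Cutting the random intervention sample to about 75 to 78 per practice (900 to 936 people) would save mailings but is optional. It is a trade-off, since expected new-AF respondents from the sample with a baseline would fall from about 23 to about 14.

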### Data management

Data sent from practices to the trial team will be labelled with participant ID number (link-anonymisation), initials and partial date of birth. The local investigator at each site is responsible for case report form integrity. We will offer secure online data capture (including e-consent), using an established secure system that complies with sponsor security policies (Qualtrics.^64^

ECG traces on the Zenicor system will be labelled with participant ID number, initials and partial date of birth.

Participant questionnaires will be link-anonymised and returned to the trial team by post or online prior to checking and entering.

Participant identifiable data will be stored, handled and processed securely and confidentially, in accordance with sponsor data security policies, UK data laws and ethical guidelines. Access will be restricted to specific members of the trial team. Further information is accessible on the trial website (https://www.safer.phpc.cam.ac.uk/).

### Statistical analysis

Data will be analysed according to Consolidated Standards of Reporting Trials principles and its extension for cluster trials.^65^ Outcomes will be analysed using an intention-to-treat principle for primary analysis. However, as both external and internal validity are important in the pilot study, secondary analysis will be conducted according to the per-protocol principle, when necessary and justified.

The proportion of those consented who took up screening, the proportion found to have AF (both new and previously known) and proportion who were anticoagulated will be calculated. The proportion of diagnoses of new AF participants in intervention and control practices and rate of anticoagulation will be compared. Clustering by practices will be accounted for with an adjusted χ^2^ test for simple comparisons and mixed effects regression models for covariates.

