### Design

A pragmatic, primary care-based, multicentre, two-parallel arm, open-label, practice-level cluster RCT which aims to recruit 12 600 participants from 36 practices in a 2:1 ratio of usual care (control) to screening (intervention). Participants will be followed up for 12 months for pilot study outcomes, and also for an average of 5 years for main trial outcomes. There will be an embedded process evaluation and qualitative studies, and an economic evaluation. The first practice was randomised on 16 April 2021. Follow-up (for the internal pilot) is scheduled to finish on 30 May 2023.

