### Outcomes

Primary and secondary outcomes are shown in box 1. The internal pilot will specifically report on outcomes that are relevant for consideration of continuation of the trial. Participants in the internal pilot study will also be followed up for an average of 5 years for main trial outcomes. The process evaluation during the pilot (protocol to be published separately) will report outcomes to guide the successful delivery of the SAFER main trial and a national-scale AF screening programme.

Box 1Primary and secondary outcomes assessed in the SAFER internal pilot studyPrimary outcome:Atrial fibrillationIn intervention practices: the number of participants that had AF detected through screening.In intervention and control practices: the number of newly detected AF patients in intervention practices compared with control practices.Secondary outcomes:Uptake of anticoagulationProportion of participants with AF detected through screening in intervention practices who were started on anticoagulation.Number of participants with newly detected AF that were started on anticoagulation in intervention and control practices.Parameters to refine the sample size calculation for the main trial (current assumptions in parentheses).Proportion of consented participants in intervention practices who are screened over the screening period (85%).Proportion of screened patients in whom newly diagnosed AF is detected (3%).Proportion of participants with newly diagnosed AF from screening who commence anticoagulation (80%).Proportion of participants with a known diagnosis of AF that is detected by screening who newly commence anticoagulation, despite previously not being prescribed anticoagulation (55%).

A random sample of participants stratified by age and sex in both intervention and control arms will be sent questionnaires to assess possible psychological effects of screening. Qualitative work will also contribute to understanding the benefits and harms of screening, and participant experience.

Our definition of newly detected AF is a first AF code recorded within twelve months of randomisation and no AF code in the GP records prior to the date the practice was randomised.

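### The two-arm anticoagulation outcome is stated in three ways that do not agree, and the wording leans towards a rate among AF patients, a group that screening itself changes

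*Protocol article*

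**What the plan says.** The protocol article describes the between-arm anticoagulation outcome in three places.

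- **Outcomes, Box 1** lists a count: "Number of participants with newly detected AF that were started on anticoagulation in intervention and control practices".
- **Follow-up data, Uptake of anticoagulation** lists a variable: "For patients diagnosed with AF, whether or not they are prescribed anticoagulation (intervention and control practices) using GP electronic data". This is not limited to new AF, and the Eligibility section deliberately admits people with known AF who are not anticoagulated.
- **Statistical analysis** gives the comparison: "The proportion of diagnoses of new AF participants in intervention and control practices and rate of anticoagulation will be compared". The second half of that sentence has no denominator. The same section sets intention to treat for the primary analysis and adjusts for clustering by practice.

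The Outcomes section defines newly detected AF by a code that first appears in the GP record in the year after randomisation. The Introduction uses anticoagulation rates to mean the treated share of eligible AF patients.

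Separately, the Aim and Box 1 name a single-arm quantity: the share of screen-detected AF in intervention practices that is anticoagulated. The planning value for new AF found by screening is 80%.

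**The concern.** Screening is meant to enlarge the group with diagnosed AF; the primary outcome tests exactly that. A treated share within that group therefore compares two differently selected sets of patients. In one arm many cases were found by screening, often without symptoms; in the other they came to light in usual care. Randomisation does not protect such a comparison, and a higher or lower share in one arm cannot be read as an effect of screening on anticoagulation.

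The question a randomised comparison can answer is how many more people, out of everyone allocated, start anticoagulation because screening was offered. Consent is complete before a practice is randomised, so all consented participants form a base that allocation cannot alter. The article does not say which of the two quantities it intends, and the two can point in opposite directions.

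**Working it through.** **1. The plan's own figure.** The Sample size section states "90% power at 5% significance level to detect a 1.1% absolute difference" for new AF. It gives no figure for anticoagulation.

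- Arm sizes, from "350 consented participants from each of the 12 intervention and 24 control practices": 12 × 350 = 4200 and 24 × 350 = 8400.
- Design effect with ICC 0.001: 1 + 349 × 0.001 = 1.349.
- Effective sizes: 4200 / 1.349 = 3113 and 8400 / 1.349 = 6227.
- A pooled-variance test of two proportions at 5% (two-sided assumed, as sidedness is not stated) gives 90.5% power for 3.0% vs 1.9%, so the stated 90% reproduces. For 2.55% vs 1.45% it gives 94.9%.

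**2. Two denominators, same data.** Inputs:

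- Screening-arm new AF: "assuming 3% newly diagnosed AF is detected in screened patients", together with the "assumption that 85% of participants per intervention practice will be screened", gives 3% × 85% = 2.55% of all intervention participants.
- Control new AF: not stated. Taken as 2.55% − 1.1% = 1.45%, which treats the detectable difference as the true one (assumption).
- Treated share of new AF, screening arm: 80% (Box 1, for screen-detected cases), applied here to all new cases in that arm.
- Treated share of new AF, control arm: not stated. Range 75% to 95% (assumption).

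Per-participant proportion = new AF × treated share. Screening arm: 2.55% × 0.80 = 2.04%. Control arm: 1.45% × share.

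| Control share | Among new AF cases (screening vs control) | Per consented participant | Difference in points | Power, per participant |
|---|---|---|---|---|
| 75% | 80% vs 75% | 2.04% vs 1.09% | +0.95 | 94% |
| 80% | 80% vs 80% | 2.04% vs 1.16% | +0.88 | 90% |
| 85% | 80% vs 85% | 2.04% vs 1.23% | +0.81 | 84% |
| 90% | 80% vs 90% | 2.04% vs 1.31% | +0.73 | 76% |
| 95% | 80% vs 95% | 2.04% vs 1.38% | +0.66 | 66% |

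The rate among cases changes sign at a control share of 80%. The per-participant proportion would change sign only at 2.04 / 1.45 = 141%, which cannot occur. Power uses the design effect of 1.349, so it assumes the same ICC for this outcome.

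**3. Other assumptions.**

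- *New AF of 3.0% vs 1.9%*, the pair that reproduces the stated power, with control share 85% to 90%: 3.0% × 0.80 = 2.40% vs 1.9% × 0.85 to 0.90 = 1.62% to 1.71% per participant. Among cases it is still 80% vs 85% to 90%.
- *Screening adds 2.55% to a background of 1.0% in both arms*, with 90% of background cases treated: per participant 2.55% × 0.80 + 1.0% × 0.90 = 2.94% vs 0.90%. Among cases, 2.94 / 3.55 = 82.8% vs 90.0%.
- *Known untreated AF included*, as the follow-up wording allows. Assume 1% prevalence, 55% starting if screened (Box 1), 10% starting otherwise, and 80% of new AF treated in both arms. Screening: (2.04% + 1% × (0.85 × 0.55 + 0.15 × 0.10)) / 3.55% = 2.52 / 3.55 = 71%. Control: (1.16% + 0.10%) / 2.45% = 51%. Here the rate among AF patients favours screening.

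The rate among AF patients can thus favour either arm, depending on who counts as an AF patient and on a control share that the article does not give. The per-participant proportion favours screening in every case shown.

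**The case against.** The strongest reply is that the article never commits to the AF-only denominator. The comparison sentence names none. The follow-up section lists what is collected, and that information is also needed to build a sound numerator. The Box 1 count is that numerator and fits an all-participant base, as does the stated intention-to-treat principle. An article may also leave the exact denominator of a secondary outcome to the full protocol or analysis plan. Much of this stands: silence alone would not be a finding. But the article is not merely silent. Its three statements do not agree, and the only one that names a population for the two-arm variable names a group formed after randomisation.

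A reader might be tempted by four stronger readings. The document does not support them.

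- *Screening will appear to lower anticoagulation.* This needs a control treated share above that of the screening arm. The article gives no such share, and says only that anticoagulation is still below what it should be.
- *The decision to proceed is compromised.* The Aim names uptake in screen-detected AF, a single-arm proportion. It is legitimate for that purpose and for the main trial's sample size.
- *Raw counts will be compared under 2:1 allocation.* With 80% treated in both arms the counts would be 4200 × 2.04% = 86 vs 8400 × 1.16% = 97, against the direction of the proportions. But the planned adjusted χ² test and mixed models need denominators, and with the 1.0% background case above the counts are 123 vs 76, with no reversal.
- *The primary outcome is mis-specified as a number.* The Sample size and Statistical analysis sections both treat it as a proportion, so Box 1 is only a wording mismatch.

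**Conclusion.** The point holds as an inconsistently defined between-arm outcome whose most natural reading is not a randomised comparison. On the planning figures and an assumed control new-AF rate of 1.45%, the rate among new AF cases would run from 5 points in favour of screening to 15 points in favour of control as the assumed control treated share goes from 75% to 95%. Over the same range the per-participant difference stays between +0.95 and +0.66 points in favour of screening. The control AF rate and the control treated share are both assumptions, so the figures show that the choice of denominator can decide the sign, not that it will. The effect is confined to a secondary outcome.

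**What to change.** In the Statistical analysis section and Box 1, define the between-arm outcome as the proportion of all consented participants in randomised practices, without a prior AF code, who have newly detected AF and start anticoagulation within 12 months. Analyse it by intention to treat with adjustment for clustering. Prior AF coding is fixed before randomisation, so this restriction keeps the comparison randomised.

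Show starts among participants with known untreated AF as a separate outcome over all consented participants. The trial includes these people on purpose, and the new-AF outcome would otherwise miss them. Report the treated share among AF cases by arm descriptively only. Keep the single-arm uptake in screen-detected AF as it is. Reword the two-arm primary outcome in Box 1 as a proportion, to match the Statistical analysis section.

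The cost is a few sentences of outcome and analysis wording. The data are already to be taken from GP records in both arms.

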### Randomisation and allocation

On the day after the recruited and consented participant target number is reached for a practice (350 participants), we will close recruitment and the practice will be randomised, stratified by practice location deprivation score^52^ and prevalence of AF reported in the Quality and Outcomes Framework. No recruitment will take place in a practice once randomisation has occurred.

Randomisation will be implemented using a secure online randomisation system (Sortition^53^) hosted by the University of Oxford Clinical Trials Unit. Practices will be randomised using random permuted blocks within nine strata corresponding to three groups (tertiles) of practice location deprivation score and three groups (tertiles) of practice-level prevalence of AF. The block sizes will be known only to the trial statistician and the randomisation system programmer. All activity on the programme will have an audit trail.

Blinding of allocation to the trial team and to the practices will not be possible.

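### Practices are randomised within nine strata, but the clustering-adjusted chi-squared test leaves them out and the planned mixed models do not name them; a small gain in precision is forgone (minor)

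*Protocol article*

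**What the plan says.** Under Randomisation and allocation: "Practices will be randomised using random permuted blocks within nine strata corresponding to three groups (tertiles) of practice location deprivation score", crossed with three groups by practice-level AF prevalence.

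Under Statistical analysis, new AF and anticoagulation are to be compared between intervention and control practices. The method follows in one sentence: "Clustering by practices will be accounted for with an adjusted" chi-squared "test for simple comparisons and mixed effects regression models for covariates". The adjustment named is for clustering only. The section does not say which comparisons count as simple, which covariates enter the models, or which of the two methods is primary.

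Under Sample size, the design is "350 consented participants from each of the 12 intervention and 24 control practices", giving "90% power at 5% significance level to detect a 1.1% absolute difference in the frequency of diagnosis of new AF", with an intraclass correlation of 0.001. No allowance is made there for stratification.

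**The concern.** Stratified randomisation balances the arms on differences between strata. A test that corrects only for clustering still counts those differences as between-practice noise. If deprivation and recorded AF prevalence are related to new AF, the standard error is then too large, the confidence interval too wide and the test conservative.

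A second, smaller reason to adjust is residual imbalance. Thirty-six practices over nine strata average four each, while blocks that hold a 2:1 ratio must have a length divisible by three. Some strata are therefore likely to end on an incomplete block. A model containing the stratifiers corrects for that; the chi-squared test does not.

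At stake is some precision in the between-arm comparison of new AF, which is part of the primary outcome and informs the decision to proceed to the main trial.

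**Working it through.** **Inputs from the protocol article.** 12 intervention and 24 control practices of 350 (4200 and 8400 participants); ICC 0.001; difference 1.1 percentage points; 5% significance; 3% detection in screened patients; 85% screened.

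**Assumptions.** Two-sided test. The control rate is not stated, so two pairs are used: 3.0% v 1.9%, and 0.85 × 3% = 2.55% v 1.45%. The share R² of between-practice variance explained by the strata is not given and is varied from 0 to 100%.

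**Step 1: reproduce the stated power.** Design effect = 1 + 349 × 0.001 = 1.349. Effective sizes are 8400/1.349 = 6227 and 4200/1.349 = 3113. A two-proportion test with pooled variance at 3.0% v 1.9% gives 90.5%, with a detectable difference at 90% power of 1.09 points. The pair 2.55% v 1.45% gives 94.9%. The stated 90% therefore follows from the plain design effect with no gain from strata.

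**Step 2: let the strata explain a share R².** The design effect becomes 1 + 349 × 0.001 × (1 − R²), and the standard error without strata is too large by √(1.349 / adjusted design effect). For example, at R² = 25%: √(1.349/1.262) = 1.034. Degrees of freedom are 36 − 2 = 34 without strata and 30 with two tertile main effects (4 parameters). Power is at 3.0% v 1.9%.

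| R² | Design effect | SE ratio | Power, normal | Power, t on 30 df |
|---|---|---|---|---|
| 0 | 1.349 | 1.000 | 90.5% | 85.8% |
| 25% | 1.262 | 1.034 | 92.1% | 88.0% |
| 50% | 1.175 | 1.072 | 93.7% | 90.1% |
| 100% | 1.000 | 1.161 | 96.5% | 94.0% |

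The comparator for the last column is 86.0%: no strata, t on 34 df. The t-based figures use unpooled variance as well as a t reference, so they should be compared with each other and not with the normal column.

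**Step 3: simulation.** Cluster-level, ICC 0.001, 6000 runs per setting, nine strata of four practices and blocks of three (both assumed), strata fitted as two tertile main effects. Type I error is at a common rate of 1.83%, power at 2.55% v 1.45%.

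| R² | Type I error, without / with strata | Power, without / with strata |
|---|---|---|
| 0 | 5.5% / 5.2% | 95.1% / 94.6% |
| 25% | 4.4% / 5.1% | 94.9% / 95.1% |
| 50% | 4.2% / 5.1% | 94.9% / 95.7% |
| 100% | 2.8% / 5.1% | 96.2% / 98.3% |

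The Monte Carlo standard error of a 5% rejection rate is √(0.05 × 0.95/6000) = 0.28 points. The direction agrees with Step 2. At 25 to 50% explained, the simulated power gain is under one point.

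**The case against.** The strongest reply is that the sentence on methods offers two tools, and the second, a mixed-effects model, can carry the stratifiers. A reader might infer that the plan excludes the strata or fixes the chi-squared as the primary test. The text supports neither: it does not define a simple comparison, list covariates or rank the methods. Those details may sit in a full protocol or SAP that is not shown, and their absence from a condensed article is not in itself a fault. This stands, and it limits the point. What remains is that the one test described for simple between-arm comparisons is adjusted for clustering alone, although the randomisation is stratified.

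A reader might also infer that planned power is lost. It is not: the 90% reproduces from the unstratified design effect. Nor is a benefit from adjusting certain. The article gives no reason for its choice of stratifiers and no figure for how well they predict new AF. High recorded prevalence could reflect thorough past detection as much as a high future yield. If the strata explain nothing, adjusting costs a little power.

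Finally, any error is on the conservative side, and the screening-arm counts and proportions in Box 1 (uptake, yield, anticoagulation after screening) are untouched by this test. That stands too, and is why the point is minor.

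**Conclusion.** The point holds as a minor mismatch between design and analysis. If the strata predict new AF, the clustering-adjusted chi-squared is mildly conservative. At ICC 0.001 its standard error is 3 to 7% too large if they explain 25 to 50% of between-practice variance, with a ceiling of 16% if they explain all of it. Over the 25 to 50% range, simulated type I error is 4.4 to 4.2% in place of about 5%. The power forgone is under one point in simulation at 2.55% v 1.45%, and about 2 to 4 points by formula at 3.0% v 1.9%.

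These sizes rest on an assumed share explained, assumed control rates and the planned ICC. The direction depends only on the strata being prognostic. Neither the validity of the comparison nor the planned 90% power is in question.

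**What to change.** State that the primary between-arm analysis of new AF is the already planned mixed-effects model, or an equivalent practice-level analysis. It should include deprivation tertile and AF-prevalence tertile as fixed main effects and use small-sample, between-practice degrees of freedom. Keep the adjusted chi-squared as a supporting analysis. Main effects are preferable to nine separate cells because they use 4 parameters and leave 30 degrees of freedom, against 26.

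The cost is a change of wording before analysis. No new data are needed, since both variables are used at randomisation. The downside is the 4 degrees of freedom out of 34. If the strata explain nothing, power falls by about half a point in simulation (95.1% to 94.6%) and by 0.2 points on the t-based formula (86.0% to 85.8%). If a fuller protocol or SAP already specifies this, a short statement to that effect closes the point.
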